### Questionnaire 2) mental health General knowledge and e Attitudes to Mental disorders/Illnesses

The mental health general knowledge questionnaire consists of 28 questions responded to on a 3-point scale (“True”, “False”, or “I don't know”) based on the six modules of the guide. The Attitudes to Mental Illness Questionnaire consists of 8 questions including include statements about mental disorders or people with a mental illness and ask respondents to express their level of agreement using a Likert scale (from "strongly disagree" to "strongly agree"). Mcluckie, Kutcher [14]evaluated the mental health general knowledge questionnaire and attitudes to mental illness, and Cronbach's alpha 0/71 was confirmed.

### Data analysis

To describe and analyze data, descriptive and inferential statistical methods are utilized. Qualitative variables will be presented as frequency and percentage, while quantitative variables will be presented as mean and standard deviation. The paired t-test will be used to measure the significant difference in mental health literacy, knowledge, and attitude between the before and after surveys. *p* < 0.05 will be considered as a significant level. SPSS software (version 26) will be used for analysis.

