### Population and sampling

The study population includes all adolescents in grade 8th and 9th year of secondary schools (13 to 15 years old) using stratified random sampling from Sirjan city; a city in Kerman province in the southeast of Iran. Using the effect size and primary data of Nguyen, Dang [17] study and considering the first type error at the level of 0.05 and the power of 0.80, the sample size was calculated to be 281 students in each of the intervention and control groups. Finally, 562 students of the first secondary schools of Sirjan city will be included in the study.$${n}_{1}={n}_{2}=\frac{\left({S}_{1}^{2}+{S}_{2}^{2}\right){\left({Z}_{1-\frac{a}{2}}+{Z}_{1-\beta }\right)}^{2}}{{\left(\overline{{X }_{1}-\overline{{X }_{2}}}\right)}^{2}}$$

After receiving the list of first secondary schools from the Department of Education, in order to prevent the effect of the intervention and based on the three geographic regions of Sirjan, a total of 20 first secondary schools will be randomly divided into two groups of control and intervention. This number of schools was determined based on the assumption that each school has a minimum of 28 students to be included in the study. According to the procedure for implementing the intervention, two teachers (a health coach and an educational coach) will be chosen from each school. Twenty teachers from each of the two groups (intervention and control) will take part in the study, for a total of 40 teachers. If a teacher expresses unwillingness, will be replaced by another teacher.

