### Implementation of Phase II

#### Step 1) Pre-test

This component is intended to help the teacher with self-study before using the guide in the classroom. Participating in the pre-test assists in identifying areas where the teacher's knowledge base needs to be expanded. Following the participation, questions with incorrect answers are recorded. Then, the teacher's mental health literacy will be strengthened using the guide's educational resource. The post-test is administered following the completion of the teacher's mental health literacy empowerment. The pre- and post-test questionnaires for teachers will be mental health literacy and mental health general knowledge questionnaires. Questionnaires will be completed again two months later.

Teachers (control and intervention groups) will complete the Mental Health Literacy Scale (MHLS) and general mental health knowledge prior to the implementation of the program. Also, Students (control and intervention groups) complete questionnaires assessing mental health literacy, general knowledge of mental health, and attitudes toward mental disorders, in addition to a demographic information form. Lastly, the participants will decide when the best time is to hold the educational intervention classes.

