### Step 3: Application of an educational program for students based on the Guide Cymru

Prior to the start of study, written consent will be obtained students' parents. Teachers will provide informed consent forms to parents. To keep the confidentiality and anonymity, consent forms will be gathered, and the study team will develop an identification code for each student, which will be completed by teachers. It is worth mentioning that this code will be will be used in student evaluation. Participants are also assured that their personal information will be kept strictly confidential. The evaluation is based on three questionnaires measuring mental health literacy, general knowledge of mental health, and attitudes toward mental disorders, allowing the teacher to assess the significant dimensions of mental health literacy. Before teaching the guide in the classroom, the pre-test will be administered; following the completion of the sixth module, the post-test will be administered again; and two months later, the questionnaires will be administered once more. Students will attend sessions on the specified day and time depending on the allocated groupings. Following the pre-test, a qualified teacher will lead an educational content session of the school-based mental health literacy program based on the six modules under the supervision of the researcher and psychologist. The Guide training consists of six modules taught sequentially over the course of eight to ten sessions. The modules are constructed in such a manner that each one is conducted in 60-min lessons. Among all modules of the Guide, the third module is the longest and most informative module, requiring more teaching time than the others. As a result, three 50-min intervals will be allotted to this module. In the control group, the general content of the Guide Cymru educational program will be presented by a psychological expert with the coordination of teachers and students. Finally, after the evaluation of the school-based mental health literacy program, teachers and pupils in the control group will receive the Guide Cymru program guide.

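### Student pre-test scores are collected in both arms but used only by subtraction in a paired t-test; the main analysis should compare the arms with the pre-test as a covariate

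*Protocol article*

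**What the plan says.** **Collection.** Under Step 1) Pre-test, "Students (control and intervention groups) complete questionnaires assessing mental health literacy, general knowledge of mental health, and attitudes toward mental disorders". Step 3 fixes the timing: "Before teaching the guide in the classroom, the pre-test will be administered", followed by a post-test after the sixth module and a repeat two months later. Each student therefore has a baseline value on each of the three scales, in both arms.

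**Analysis.** Data analysis names a single inferential method: "The paired t-test will be used to measure the significant difference in mental health literacy, knowledge, and attitude between the before and after surveys". It mentions no between-arm comparison and no use of the pre-test other than pairing.

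**Design.** Under Population and sampling, "the sample size was calculated to be 281 students in each of the intervention and control groups", with the inputs described as "considering the first type error at the level of 0.05 and the power of 0.80". The printed formula is the two-sample formula for independent means, with a two-sided critical value. The same section says that "a total of 20 first secondary schools will be randomly divided into two groups of control and intervention".

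**The concern.** A paired t-test is a test of the mean after-minus-before difference, so it fixes the slope of post-test on pre-test at 1. Done within an arm, it answers whether scores moved in that arm, not whether the programme moved them more than the control condition did. The design and the sample size formula are built for the second question.

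The only quantity that the plan supplies for that question is the raw change. The natural repair, comparing mean changes between arms, would keep the slope at 1. When the true slope is below 1, this over-corrects for the pre-test and adds noise to the treatment contrast. The baseline data that could remove the noise will already be in hand. At stake is precision in a trial of only 20 schools.

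**Working it through.** **Inputs from the article (Population and sampling).** Two-sided alpha 0.05; power 0.80; 281 students per arm; 20 schools, taken as 10 per arm; "each school has a minimum of 28 students to be included in the study" (562/20 = 28.1 on average).

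**Not in the article.** The means and SDs behind the sample size come from elsewhere ("Using the effect size and primary data of" an outside study) and are not printed. No pre/post correlation and no intraclass correlation (ICC) is given. Rho is therefore assumed over 0.3 to 0.8, with equal pre and post SDs.

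**Step 1: the plan's own figure.** Without means and SDs, 281 cannot be reproduced forwards. Solved backwards with equal SDs:

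d = (1.96 + 0.8416) × √(2/281) = 2.8016 × 0.0844 = 0.236 SD.

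Putting 0.236 back into the formula returns 281 per arm and power 0.80.

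**Step 2: variance of the two contrasts**, per student, in units of the outcome variance:

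- raw change: 2(1 − rho)
- adjusted for the pre-test: 1 − rho²
- ratio, adjusted to change: (1 + rho)/2, a reduction of (1 − rho)/2

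**Step 3: power** at 281 per arm and d = 0.236, students treated as independent: Φ(2.8016/√V − 1.96), where V is the variance from Step 2.

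| rho | V, change | V, adjusted | Reduction | Power, change | Power, adjusted |
|---|---|---|---|---|---|
| 0.3 | 1.40 | 0.91 | 35% | 0.66 | 0.84 |
| 0.5 | 1.00 | 0.75 | 25% | 0.80 | 0.90 |
| 0.7 | 0.60 | 0.51 | 15% | 0.95 | 0.975 |
| 0.8 | 0.40 | 0.36 | 10% | 0.993 | 0.997 |

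For example, at rho 0.5 the adjusted power is Φ(2.8016/0.866 − 1.96) = Φ(1.275) = 0.90. Below rho 0.5 the change score is worse than ignoring the pre-test altogether, because V exceeds 1. In sample-size terms, the adjusted analysis matches a change-score analysis of 281 per arm with 183, 211 or 239 per arm at rho 0.3, 0.5 or 0.7 (281 × 0.65, 0.75 and 0.85, rounded up).

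**Step 4: chance imbalance is the same quantity.** Given a pre-test difference B between arms, the change contrast shifts by −(1 − rho)B. For B = 0.1 SD that is −0.07, −0.05 or −0.03 SD at rho 0.3, 0.5 or 0.7. The extra variance of the change score is 2(1 − rho) − (1 − rho²) = (1 − rho)², which is exactly the variance that this shift contributes. At rho 0.5: 1.00 = 0.75 + 0.25. The chance SD of B is √[(2/10)(ICC + (1 − ICC)/28.1)]: 0.084 SD at ICC 0, 0.129 at an assumed 0.05 and 0.162 at an assumed 0.10.

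**Step 5: does clustering overturn it?** With ICC 0.01 to 0.10, school-level correlation 0.3 to 0.8 and student-level correlation 0.5 to 0.7 (all assumed), the reduction runs from about 11% to 33%. The relative gain survives. The absolute powers in Step 3 do not: at ICC 0.05 the design effect is 1 + 27.1 × 0.05 = 2.355, and an unadjusted post-score comparison drops from 0.80 to about 0.45 by the normal approximation.

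**The case against.** **The harm belongs to an analysis that the article does not plan.** In a within-arm paired t-test, a pre-test difference between arms does not enter, and no between-arm test of changes is stated. This stands, so the variance loss is conditional on the arms being compared. The condition is not far-fetched: the trial is randomised and controlled, and its sample size is computed for a difference between two arms.

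**Covariate choice is detail that a short article may leave to the analysis plan.** On its own, a missing covariate would be a weak point. But the article is not silent here. It names a specific test, and that test is a poor choice for data collected at three times in two randomised arms.

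**Readings that go too far.** A reader might infer the following, but the article does not support them:

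- *A quarter of the variance is lost.* That holds only at rho = 0.5, and no rho is given.
- *The result will be biased by baseline differences between schools.* Under randomisation a change-score contrast is unbiased. Step 4 shows that imbalance is the extra variance seen in a given sample, not a second harm.
- *Adjustment lifts power from 80% to 94% at rho 0.3 or to 86% at rho 0.7.* Those figures hold the change-score analysis at 80% for every rho, which redefines 0.236 as a multiple of the change-score SD. Nothing in the article says that its SDs are SDs of changes.
- *The point covers every outcome in the trial.* It covers the students' three scales. For teachers, Step 1 lists only two scales at pre-test.

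**Conclusion.** The point holds in a conditional form. The named analysis uses the students' pre-test only by subtraction and does not compare the randomised arms. If the arms are compared on raw changes, the contrast has more variance than one with the pre-test as a covariate. Adjustment would lower that variance by an assumed 10% to 35% over rho 0.8 to 0.3. At the back-solved effect, the gain in power is 18 percentage points at rho 0.3, 10 at rho 0.5 and 2 to 3 at rho 0.7.

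These figures assume equal pre and post SDs, equal allocation, an effect of 0.236 outcome SD that the article does not state, and independent students. Clustering lowers every absolute power but leaves the direction of the comparison unchanged over the range checked. The change should be made: the gain shrinks as rho rises, but the cost is close to nothing.

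**What to change.** In Data analysis, make the main student analysis a model of the post-test score, and separately of the two-month score, on study arm and the same student's pre-test score on that scale. Include school as a random effect, with small-sample degrees of freedom for 20 schools. Fit it for each of the three student scales. Keep the paired before-after differences as descriptive summaries within each arm, not as tests of the programme.

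The cost is a sentence or two of analysis text. No new data are needed, and the software already named can fit the model. The one downside is that students without a pre-test score need a stated rule for the covariate, for example mean imputation done without reference to arm.

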### Phase 4) Evaluation of the impact of Guide Cymru's school-based mental health literacy program

According to study of improvements in students’ mental health literacy with use of a mental health curriculum in Canadian schools [13], mental health literacy, general knowledge of mental health and attitudes related to mental disorders of students and teachers before and after the implementation of the educational intervention and with a 2-month follow-up were evaluated and the results will be compared before, immediately after, and two months after the educational intervention. By comparing a student's pre-test, post-test, and two-month post-test scores, this method of evaluation enables a precise determination of student's learning.

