### Strengths and limitations

One of the study's strength is that the Guide will be localized, thereby enabling the substitution of educational content that conflicts with Iranian culture with more suitable material. Another strength is that the educational content of the mental health literacy program will be delivered by school instructors, and its efficacy will align more closely with the program's objectives. From other strengths, this study is a randomized controlled trial with an intervention and a control group, and also the most important point in this study will be the measuring tool of the MHLS questionnaire, which includes all the key components of mental health literacy.

This study also has limitations. The absence of the school-based mental health literacy program guide in the students' curriculum is one of the limitations of this study. Therefore, instructors and students may lack the cooperation necessary for the program's implementation.

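### The only test named for the outcomes is a before-after paired t-test; no comparison between the randomised arms is stated

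*Protocol article*

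**What the plan says.** The Data analysis section says that descriptive and inferential methods will be used, and then names a single test: "The paired t-test will be used to measure the significant difference in mental health literacy, knowledge, and attitude between the before and after surveys". It sets p < 0.05, which "will be considered as a significant level". It mentions no between-arm test, group-by-time term or baseline-adjusted comparison.

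The section on evaluating the programme's impact (Phase 4) runs the same way: "the results will be compared before, immediately after, and two months after the educational intervention". It justifies this by each student's change across the three surveys, and no arm is mentioned.

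The design is a two-arm comparison. Under Population and sampling, "a total of 20 first secondary schools will be randomly divided into two groups of control and intervention", and "the sample size was calculated to be 281 students in each of the intervention and control groups". The formula printed there is for a difference between two independent means. Under Strengths and limitations the article counts it as a strength that "this study is a randomized controlled trial with an intervention and a control group". The pre-test section has control students complete the same questionnaires as intervention students. The section on applying the programme to students (Step 3) gives control pupils general Guide material from a psychology expert.

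**The concern.** Schools are randomised so that control schools can show what would have happened without the programme. A paired t-test within an arm asks only whether scores moved. They can move because pupils meet the same questionnaires three times, because they grow older during the school year, or because control-type exposure to Guide content also raises scores. None of these is the effect of the programme.

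The article therefore sizes the trial for one question and names a test for another. If the named test were the basis for conclusions, a gain common to both arms could be reported as a benefit of the Guide. Finding significance in one arm and not in the other would not settle the matter, because that contrast is not a test of the difference between arms.

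**Working it through.** **1. The plan's own figure.** The inputs are alpha and power ("considering the first type error at the level of 0.05 and the power of 0.80") and 281 per arm. The means and SDs are not printed; the calculation was made "Using the effect size and primary data of" a cited study. So 281 cannot be reproduced forwards, only solved backwards.

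- With a common SD, n = 2(1.960 + 0.842)² / d².
- Setting n = 281: d = √(2 × 7.849 / 281) = 0.236.
- Putting d = 0.2364 back in returns 281 per arm, and 2 × 281 = 562 agrees with the stated total.

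The trial is thus sized to detect a between-arm difference of about 0.24 SD with 80% power. The Data analysis section contains no test of that difference.

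**2. How the paired test behaves with no programme effect.** Assumptions, none of them in the document:

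- both arms gain the same amount g (in SD units), so the true programme effect is zero;
- the pre-post correlation r is 0.3 to 0.7;
- there are 281 pupils in the arm;
- clustering by school is ignored.

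The standard error of the mean change is √(2(1 − r)/281), which is 0.0706, 0.0597, 0.0534 and 0.0462 for r = 0.3, 0.5, 0.6 and 0.7. For g above zero the chance of p < 0.05 is close to Φ(g/SE − 1.96).

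| Shared gain g | r = 0.3 | r = 0.5 | r = 0.6 | r = 0.7 |
|---|---|---|---|---|
| 0 (both tails) | 0.05 | 0.05 | 0.05 | 0.05 |
| 0.1 SD | 0.29 | 0.39 | 0.47 | 0.58 |
| 0.2 SD | 0.81 | 0.92 | 0.96 | 0.99 |

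Example: for r = 0.5 and g = 0.1, Φ(0.1/0.0597 − 1.96) = Φ(−0.28) = 0.39.

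An observed gain of 1.96 × SE is enough for significance: about 0.12 SD at r = 0.5, and 0.14 to 0.09 SD over r = 0.3 to 0.7.

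**3. Contrasting p-values between arms.** With g = 0.1 and r = 0.6, each arm is significant with probability about 0.47, independently of the other. The pattern of significant in intervention but not in control then has probability 0.47 × 0.53 ≈ 0.25, again with no programme effect.

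**4. A between-arm test on the same data.** In 4,000 simulated trials at each gain (281 per arm, r = 0.5, gains of 0, 0.1, 0.2 and 0.3 SD), a two-sample test of the change scores rejected in 4.5-5.1%. The intervention-arm paired test rejected in 5%, 38%, 92% and 99.9% respectively.

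**5. Why the replacement must carry school.** Schools are the randomised units, with 562/20 = 28.1 pupils each on average. No intraclass correlation is given. For an assumed residual value of 0.01 to 0.05, the design effect 1 + 27.1 × ICC is 1.27 to 2.36. A between-arm test that treats pupils as independent at a nominal 5% would then reject in 2 × [1 − Φ(1.96/√DE)], or about 8% to 20% of trials, with no programme effect.

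**The case against.** The article is condensed, its Data analysis section opens with a general reference to inferential methods, and a fuller analysis plan may exist. A reader might infer that the arms will never be compared. The document does not support that: it does not say the paired t-test is the only test. What it supports is that no between-arm test is stated and that the one test named does not fit the design. This goes beyond a detail left to an analysis plan, because the article fixes a specific test and Phase 4 repeats the same before-after logic. An unseen plan with a between-arm analysis would still have to be reconciled with this text.

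A reader might also infer that the control data will be discarded. The text does not say whether the paired test is run in the intervention arm, in each arm or on everyone together. Paired tests in both arms are equally consistent with it. They would use the control data, but still would not test the difference between arms.

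Finally, it is tempting to say that a significant result is to be expected even if the programme does nothing. The figures do not go that far. With no shared gain the rate is the nominal 5%, and at 0.1 SD it lies on either side of one half. Only at around 0.2 SD does a false signal become the likely outcome, and the document gives neither a gain nor a correlation.

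**Conclusion.** The point stands and should be corrected before analysis. The document pairs a two-arm, school-randomised design and a two-independent-means sample size with a before-after test that does not estimate the randomised effect. That rests on the text alone.

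The size of the risk is illustrative. With no programme effect, the false-signal rate in the intervention arm runs from 5% (no shared gain) through 29-58% (0.1 SD) to 81-99% (0.2 SD), for correlations of 0.3 to 0.7 and with clustering ignored. The significant-in-intervention-only pattern occurs in about 25% of trials at 0.1 SD and r = 0.6. Some shared gain is plausible here because both arms repeat the questionnaires and controls receive Guide material. How large it would be is unknown.

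**What to change.** In the Data analysis section, replace the paired t-test as the inferential analysis with a between-arm comparison adjusted for the pre-test score:

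- Fit a linear mixed model to the post-test and two-month scores with arm, time, arm-by-time and baseline score.
- Include a random effect for school, the randomised unit, and allow for repeated measures within student.
- Use degrees of freedom suited to 20 clusters (a Satterthwaite or Kenward-Roger approximation, for example) rather than to 562 pupils.
- Name one outcome and one time point as the primary contrast. Three student questionnaires at two post-baseline times otherwise give six contrasts with none in charge.
- Report the adjusted between-arm difference with its 95% confidence interval, and keep paired changes as description only.

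Align the Phase 4 text so that it too says the arms are compared.

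The cost is a rewritten paragraph, more analysis work, and wider intervals than a pupil-level analysis would show, because inference rests on 20 schools. No new data are needed: pre-test scores are already planned in both arms, and SPSS, the chosen software, fits linear mixed models.

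### Schools are randomised, but the only inferential test named is a student-level paired t-test that ignores school and does not compare the arms

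*Protocol article*

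**What the plan says.** Under Population and sampling the article makes the school the unit of allocation: "a total of 20 first secondary schools will be randomly divided into two groups of control and intervention". The target is "the sample size was calculated to be 281 students in each of the intervention and control groups", 562 in total, and the number of schools rests on at least 28 students in each. Two teachers come from each school, and "Twenty teachers from each of the two groups (intervention and control) will take part in the study", which implies ten schools per arm. Geography is mentioned in the same place: "based on the three geographic regions of Sirjan, a total of 20 first secondary schools will be randomly divided".

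Under Data analysis, the only inferential statement is that "The paired t-test will be used to measure the significant difference" in the literacy, knowledge and attitude scores from before to after, with significance at p < 0.05. No school term, region term or comparison of arms is named. The section on evaluating the programme's impact also describes comparisons of each student's own scores over time. Strengths and limitations nevertheless counts the randomised design with a control group among the study's strengths.

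**The concern.** Two features of the stated test do not fit the design.

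First, a paired t-test on students assumes that their change scores are independent. Students in one school share teachers, setting, survey conditions and whatever else happens there between the surveys, so their changes are likely to be correlated. The test would then count about 281 independent observations per arm where ten schools per arm were allocated, and its p-values would be too small.

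Second, the test asks whether scores changed within a group, not whether they changed more under the programme than without it. Retesting, maturation or outside events can move both arms. Control students also receive general programme content from a psychological expert, so change in that arm is plausible too. A significant before-after result in the intervention arm would not be evidence from the randomisation.

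At stake is the validity of every p-value for all three outcomes, since no other test is named.

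**Working it through.** **Inputs from the article.** Two-sided level 0.05 and power 0.80; 281 students per arm; 562 in total; 20 schools; at least 28 students per school; two teachers per school and 20 teachers per group.

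**The article's own figures.** Schools per arm: 20 teachers / 2 per school = 10. Students per school: 562 / 20 = 28.1, and 20 × 28 = 560, which agrees with 562. The 281 cannot be reproduced, because the standard deviations and mean difference in the formula are not given. Solved backwards, (1.960 + 0.842) × √(2/281) = 0.236, so 281 corresponds to a standardised difference of about 0.24 with no allowance for clustering.

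**Assumed input.** The ICC of the change score is not in the article. The range used is 0.01 to 0.10.

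**Effect of ignoring school.** With m = 28 students per school:

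- design effect DE = 1 + (m − 1) × ICC = 1 + 27 × ICC
- factor by which the standard error is too small = √DE
- true level of a nominal 5% test = 2 × [1 − Φ(1.96/√DE)]

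| Assumed ICC | DE | √DE | True level |
|---|---|---|---|
| 0 | 1.00 | 1.00 | 5.0% |
| 0.01 | 1.27 | 1.13 | 8.2% |
| 0.02 | 1.54 | 1.24 | 11.4% |
| 0.05 | 2.35 | 1.53 | 20.1% |
| 0.10 | 3.70 | 1.92 | 30.8% |

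**Simulation check** (20,000 runs, 10 schools of 28 per arm, no true effect). The columns are rejection rates at a nominal 5%.

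| Assumed ICC | Paired t-test within one arm | Student-level two-arm t-test on change | t-test on 20 school means (18 df) |
|---|---|---|---|
| 0.01 | 7.9% | 8.1% | 4.9% |
| 0.02 | 11.4% | 11.1% | 5.0% |
| 0.05 | 20.1% | 20.5% | 5.2% |
| 0.10 | 31.2% | 31.0% | 5.0% |

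**What the paired test cannot separate.** Assume no programme effect but a before-after shift common to both arms, in units of the change-score SD. With 281 students and ICC 0, a shift of 0.10 gives 0.10 × √281 = 1.68, and the test is significant with probability about 1 − Φ(1.96 − 1.68) = 39%. A shift of 0.20 gives 3.35 and 92%. At ICC 0.02 the figures are 41% and 87%. A school term alone does not cure this; a comparison with the control arm is needed.

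**Region.** With ICC 0.02, a further region share of variance of 0.02 (assumed) and allocation stratified by region, a school-level two-arm test that omits region rejects 3.2% of the time. That is below 5%, so the standard error of the arm comparison is too large, not too small.

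**Teachers.** With two per school, DE = 1 + ICC. At ICC 0.02 / 0.05 / 0.10 the true level is about 5.2% / 5.6% / 6.2%.

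**The case against.** Only an article is at hand, and a full protocol or analysis plan could contain the model. That would excuse silence, but the article is not silent: it names a specific test, and that test does not match the allocation it describes.

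A better objection is that the ICC is unknown and may be small. Taking differences removes stable differences between schools. If the programme had no effect in any school, shared delivery by the same teachers would not itself correlate the changes; only other school-level influences would. This stands as a reason to give a range rather than one figure, and to start it low. It does not rescue the test: at ICC 0.01 the level is already about 8%, only an ICC of zero gives 5%, and the lack of an arm comparison remains whatever the ICC.

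Three stronger readings may tempt a reader, and the article supports none of them.

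- That leaving out the region strata also makes standard errors too small. For the arm comparison the direction is the opposite. The wording on region is also loose: it may describe how schools are sampled or kept apart rather than stratified randomisation.
- That teacher outcomes are inflated as badly as student outcomes. With two teachers per school the effect is slight.
- That 11% to 31% is the rate of false claims of programme benefit. For the named test it is the error rate for the null of no change within an arm.

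**Conclusion.** The point holds. The Data analysis section fixes a test that ignores the unit of randomisation and makes no use of the control arm, so it is wrong as written and must be changed. The true level of the nominal 5% student-level test is about 8% to 31% for an assumed change-score ICC of 0.01 to 0.10, with ten schools of 28 per arm and equal school sizes. No single value in that range can be read from the article. The missing between-arm comparison depends on no such assumption and is at least as serious. Region is a question of precision, and the teacher part is minor.

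**What to change.** Replace the paired t-test in Data analysis with a between-arm comparison that accounts for school. Either of these would do:

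- a linear mixed model for the post-test score with arm, baseline score and a random intercept for school, using small-sample degrees of freedom such as Satterthwaite; if post-test and two-month scores are modelled together, add a student-level term for the repeated measures; or
- a comparison of baseline-adjusted school means between arms.

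State whether region was used in the allocation. If it was, include it as a fixed effect for precision. A school term for teacher outcomes is proper, though it will change little. Before-after summaries within each arm can stay as description.

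The cost is a change of wording. Where the ICC is above zero, intervals become wider but valid. The arm comparison has about 20 − 2 = 18 degrees of freedom, or 20 − 4 = 16 with two region terms. No data collection changes.
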